### Intervention group

The intervention will be given in arm-1 (intervention) group participants will receive a daily SMS text and weekly phone calls for medication intake and medication refill visit reminders. All participants will receive the intervention at a similar time for two months during the continuation phase of anti-TB treatment (Fig 2).

**Fig 2 pone.0261758.g002:**
[figure not shown]
Mobile-assisted Medication Adherence Support (Ma-MAS) intervention diagram.

### Control group

The control group (Arm-2) participants will receive the same routine standard treatment care as the intervention group, but no SMS text and phone calls intervention. Patients in the control group will be followed for the same two-month period as the intervention group during the continuation phase of their treatment.

### Intervention development procedure

The mobile SMS text messages will be developed systematically with the best available evidence in the context area and with the application of appropriate behavioural theory and technique. The intervention will be developed and evaluated based on the Medical Research Council (MRC) framework for complex interventions in healthcare (Table 1) [40]. The non-sequential development stage of the framework as adapted by Bleijenberg et al. (2018) will be used as a more specific guide for the intervention design [41]. This has seven different phases:

        Phase 1: problem definition (identification and analysis)        Phase 2: systematically identifying the evidence        Phase 3: identifying and developing a theory        Phase 4: determining the needs (patients and/or providers)        Phase 5: examining the practice        Phase 6: modeling process and outcome and        Phase 7: intervention design.

**Table 1 pone.0261758.t001:** Mobile-assisted medication adherence support intervention development process using an adapted development phase of MRC framework and the associated methods.

Development phases	Methods
Phase 1: Problem identification and definition	• Review of literature • Qualitative research
Phase 2: Identifying the evidence base	• Review of literature • Qualitative research • Quantitative Survey research
Phase 3: Identifying and/or developing theory	• Review of literature
Phase 4: Determine the need	• Review of literature • Qualitative research
Phase 5: Examine current practice and context	• Qualitative research
Phase 6: Modeling process and outcome	• Modeling a prototype of intervention components • Identity interrelation with the outcome • Experts opinion through Delphi method and survey
Phase 7: Intervention design	• Experts opinion • Refine the intervention

#### Phase 1: Problem identification and definition

The problem of non-adherence to the anti-TB medication has been identified and defined through a literature review. The literature review is published in the title of “Factors Influencing Patient Adherence to Tuberculosis Treatment in Ethiopia? A Literature Review” [6]. This review will be further supported by qualitative research using in-depth interviews with TB patients and healthcare providers.

#### Phase 2: Identifying the evidence base

Evidence has been collected through a review of literature, to identify the effectiveness of mobile health SMS interventions including acceptability, feasibility, and characteristics of the intervention. Acceptability and feasibility survey will be conducted before the trial is implemented. This phase aims to identify previous interventions and their effectiveness and to assess the acceptability and feasibility of the target groups of the interventions, as well as the success and failure factors (S1 and S2 Tables).

#### Phase 3: Identifying and/or developing theory

The theories or models that can best explain the proposed intervention mechanism and action have been selected through a review of the literature. This phase of development aims to identify the theory or model that can best explain the intervention mechanism of action. We have selected an information motivation behavioural skill model [42], and have shown the relationship between the model construct of information, motivation and behavioural skills with adherence behaviour based on the factors affecting TB medication adherence identified in phase one (Fig 3).

**Fig 3 pone.0261758.g003:**
[figure not shown]
Information, motivation and behavioural skills model to Tuberculosis medication adherence adapted from Fisher et al. 2006 [42].

#### Phase 4: Determine the needs

The needs, preferences, perceptions, and capacities of the patient and healthcare providers with the identified problems and proposed solutions will be determined through a review of the literature and qualitative research by using in-depth interviews. This will generate information about which characteristics of the intervention are likeable and adaptable, and how the SMS texts can be tailored regarding language, content, frequency, length, and time of the day.

#### Phase 5: Examine current practice and context

Identification of barriers and facilitators of mobile health interventions through examining the current practice and context from the patient’s and healthcare provider’s perspectives will be made. This would help the functionality of the proposed mobile health intervention best fits with the existing practice and context. This activity will be done through qualitative research by using in-depth interviews.

#### Phase 6: Modelling process and outcome

Modeling the active component of the mobile health intervention and its relationship with outcomes will be refined with multidisciplinary team involvement. The initial SMS text content will be refined using the taxonomy of evidence-based behaviour change [43]. The Delphi technique will be employed to validate the content of the SMS text further. Eight experts from different professional backgrounds of behavioural science, healthcare system, pulmonary disease, and digital health experts will be involved in this process. A survey will be conducted among health professionals who working as TB focal persons and communicable disease control officers from health facilities and health offices in Addis Ababa, Ethiopia.

#### Phase 7: Intervention design

A full prototype mobile SMS text intervention will be developed and will be given to experts for their feedback to make final refinements. The experts will be asked to comment on the timing and frequency of information, clarity, and arrangement of the SMS text messages. Based on the expert’s comments the final SMS text message set will be prepared.

### Outcome

The outcome of the trial is the medication adherence of the patient, measured by both direct and indirect methods of measurement. The primary outcome will be measured using an IsoScreen test (GFC Diagnostics Ltd, Bicester, England) for the presence of isoniazid (INH) drug metabolites in urine in accordance with the vendor-supplied user manual. The IsoScreen test result is negative when there is no colour change (i.e. the strip remains yellow) after 5 minutes, and the test result is positive when the colour changes to dark purple, or blue/ green in that time, depending on the concentration of the medication (i.e. if the medication was taken in the last 24 hours or 48 hours respectively) [44, 45]. The IsoScreen test will be done at the fourth and eighth weeks of the intervention. The proportion of adherence measured by the IsoScreen test at the eighth week of the intervention (primary end point) will be used as the primary interest of analysis. The proportion of adherence measured by the IsoScreen test at the fourth week of the intervention will be used as the secondary interest of analysis.

The secondary outcome will also be measured by self-report of medication adherence using the adapted AIDS Clinical Trial Group adherence questionnaire (ACTG) [46], Visual Analogue Scales (VAS) [47], and by clinic appointment attendance registration [48]. The adapted version of ACTG has three sections: section B (social support), section C (possible reasons for non-adherence) and section D (adherence behaviour). Participant scores less than “somewhat satisfied” to any questions in section B or other than “never” to any questions in sections C and D are considered as non-adherence [48]. VAS is a single adherence scale that requires a patient to estimate their adherence level from 0% to 100%: 0% means the patient has taken no medication, 50% means the patient has taken half of their prescribed medications, and 100% means the patient has taken all of their prescribed medications, for the last 30 days. Participant scores less than 90% for VAS are considered as non-adherence [36, 49]. Clinic appointment attendance registration for weekly medication refills visits will also be used for adherence measurement. Patients who delay for at least one medication refill visit are considered as non-adherence [48]. The ACTG and VAS questions will be asked at bassline assessment and end of two months of intervention (Fig 1). The proportion of adherence measured by self-report and clinic appointment attendance registration at the eighth week of the intervention will be used as the secondary interest of analysis.

### Sample size

A STATA code *power twoproportions* was used to calculate the sample size considering the trial outcome of anti-TB medication non-adherence. The rate of anti-TB medication non-adherence in Ethiopia varies considerably in the literatures, ranging from 10% to 26% depending on the patient’s treatment phase and different settings [8, 11, 14]. It was found specifically that the rate of non-adherence was 25.6% (po = 0.256) during the continuation phase of treatment from a recent study conducted at Addis Ababa, Ethiopia [14] in the control group. We used a 15% absolute reduction of non-adherence due to a mobile SMS text intervention found in a similar study [37] to estimate a non-adherence rate of 10.6% (pa = 0.106) in the intervention group. Considering that we are using a simple randomized controlled trial parallel-group design, choosing a 95% confidence level (alpha = 0.05), 80% power (beta = 0.80) and a one-sided p-value of 0.025 for the initial sample size would yield n = 81 participants per arm. Assuming an attrition rate of 15%, the final sample size would be a total of n = 186 with each of the 2 arms having n = 93. From 10 sub-cities in Addis Ababa, a total of 36 primary public health facilities will be included in the trial study by random selection, based on the assumption that on average 6 patients per public health facility will be available to be included in the study.

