### Randomization and allocation

Participants will be centrally randomized into one of the two groups using simple randomization in computer-generated algorithm, with an equal allocation ratio (1:1), by members of the research support team, who will not be involved in measuring the outcome (Fig 4).

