### Statistical analysis

The electronically collected data will be exported to STATA and cleaned using STATA coding programing language. Descriptive statistics of mean, standard deviation, median, and range will be used for continuous variables and frequency and percentage for categorical variables.

Intention to treat (ITT) analysis will be performed for all randomized participants according to their group. A chi-square test for binary outcomes and Student’s t-test for continuous outcomes will be used as appropriate. For primary and secondary interest of analysis, multivariable regression model analysis will be employed to adjust confounding factors in the statistical effect. A P-value of less than 0.05 will be used as a cut-off point to show a statistically significant association between Ma-MAS intervention and medication adherence with a 95% confidence interval.

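### The 81 per arm follows from a one-sided 5% test, not the stated one-sided 0.025; at the stated level the design has about 70% power, not 80%

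*Protocol article*

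**What the plan says.** The Sample size section names the tool and the outcome: "A STATA code *power twoproportions* was used to calculate the sample size considering the trial outcome of anti-TB medication non-adherence". It takes the control rate from an earlier Addis Ababa study, in which "the rate of non-adherence was 25.6% (po = 0.256) during the continuation phase of treatment", and subtracts 15 percentage points "to estimate a non-adherence rate of 10.6% (pa = 0.106) in the intervention group". The error rates are set by "choosing a 95% confidence level (alpha = 0.05), 80% power (beta = 0.80", and the sentence ends by saying that "a one-sided p-value of 0.025 for the initial sample size would yield n = 81 participants per arm". A 15% attrition allowance then brings the total to 186, or 93 per arm. The Randomization and allocation section confirms two arms "with an equal allocation ratio (1:1".

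The Statistical analysis section plans a chi-square test for binary outcomes and multivariable regression. Its decision rule is: "A P-value of less than 0.05 will be used as a cut-off point to show a statistically significant association", accompanied by a 95% confidence interval. It does not say in words whether the test is one-sided or two-sided, and nowhere does it announce a one-sided test at 5%.

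**The concern.** A one-sided test at 0.025 and a two-sided test at 0.05 share the critical value 1.960, so the sample-size paragraph and the analysis rule point to one and the same calculation. The 81 per arm looks too small for it. It looks like the result of asking for a one-sided test while alpha stayed at 0.05, although the document cannot show which settings were entered.

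If so, the trial's size rests on a more lenient test than the one to be run, and 80% power is claimed for a design that lacks it. The chance of missing the 15-point effect would be about 30% rather than 20%. The article describes existing evidence on SMS interventions as inconsistent and addresses its result to policymakers. A null result presented as coming from an 80%-powered trial could be misread as good evidence of no effect.

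**Working it through.** **Inputs** (Sample size section, with 1:1 allocation from Randomization and allocation)

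- p0 = 0.256, p1 = 0.106, so d = 0.150 and the mean rate is 0.181
- power 80%, so z_b = 0.8416 (the paragraph prints "80% power (beta = 0.80", but 0.80 is the power; beta is 0.20)
- one-sided 0.025, so z_a = 1.960; the alternative tested is one-sided 0.05, z_a = 1.645

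**Formula** (pooled-variance chi-square comparison of two proportions)

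n per arm = [z_a × sqrt(2 × 0.181 × 0.819) + z_b × sqrt(0.256 × 0.744 + 0.106 × 0.894)]² / d²

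The two square roots are sqrt(0.29648) = 0.5445 and sqrt(0.28523) = 0.5341.

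**Step 1: reproduce the plan's 81.** With z_a = 1.645: (0.8956 + 0.4495)² / 0.0225 = 1.8093 / 0.0225 = 80.41, so 81. The plan's figure is matched exactly, at one-sided 0.05.

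**Step 2: use the stated level.** With z_a = 1.960: (1.0672 + 0.4495)² / 0.0225 = 2.3003 / 0.0225 = 102.24, so 103.

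**Step 3: try other formulas.** None rescues 81 at the stated level.

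| Method, 80% power | One-sided 0.025 | One-sided 0.05 |
|---|---|---|
| Pooled chi-square | 103 | 81 |
| Unpooled variance | 100 | 79 |
| Arcsine | 100 | 79 |
| Likelihood ratio | 101 | 80 |
| Continuity-corrected | 116 | 94 |

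The smallest value at one-sided 0.025 is still 100 − 81 = 19 per arm above the plan. A two-sided reading of 0.025 makes the gap larger (124 by the pooled formula).

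**Step 4: power of the planned sample at the stated level.** Power = Phi[(d × sqrt(n) − 1.960 × 0.5445) / 0.5341].

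| Evaluable per arm | Source | Power | Exact enumeration of the chi-square test |
|---|---|---|---|
| 79 | 93 × 0.85 = 79.05 | 69.1% | 70.9% |
| 81 | the plan's target | 70.2% | 71.1% |
| 93 | no loss at all | 76.1% | 77.1% |

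For n = 81: (1.3500 − 1.0672) / 0.5341 = 0.5295, and Phi(0.5295) = 0.702. As a cross-check, solving the formula for 70% power at two-sided 0.05 also returns 81 (80.67, rounded up).

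**Step 5: what 80% power would take.** With 79 evaluable per arm, the difference must be about 16.7 points (25.6% versus 8.9%). To keep 15 points, 103 evaluable per arm are needed. Allowing for 15% loss, 103 / 0.85 = 121.2, so 122 per arm and 244 in total. The plan's own inflation is by multiplication (81 × 1.15 = 93.15, taken as 93); on that method 103 × 1.15 = 118.45, so 119 per arm and 238 in total. The difference between 244 and 238 is a separate matter of attrition method, not part of this error.

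**The case against.** The best defence is that 0.025 is the slip. The sentence also prints alpha = 0.05, the hypothesis is directional, and the analysis section does not name the sidedness of its P < 0.05. If a one-sided 5% test was meant throughout, 81 and 80% agree. This is the weaker reading. The 0.025 is explicit and attached to the one-sided test, and both the 95% confidence level in the sample-size paragraph and the 95% interval in the analysis fit two-sided 0.05. The fair residue is that sidedness is implied rather than stated, and should be written down.

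A second objection is that about 70% assumes the full planned loss, while the intention-to-treat analysis is to cover everyone randomised. That is correct as a qualification: the range is 69% to 76%, depending on retention. Its upper end is still below 80%.

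Third, these figures describe an unadjusted chi-square test, whereas regression adjustment is also planned. They are therefore approximate. The plan claims no gain from adjustment, and its own derivation is the unadjusted comparison.

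Finally, the type I error, the effect estimate and its interval are untouched by this mistake. That is true; the defect lies in the claimed power and in the recruitment target derived from it. A separate analysis plan could not repair it, because all the inputs and the result are printed together and do not agree.

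**Conclusion.** The paragraph is wrong as written. At one-sided 0.025 (equivalently two-sided 0.05), 80% power for 25.6% versus 10.6% needs 103 evaluable per arm; the plan has 81, a shortfall of 22 per arm. The actual power is about 70% at the planned evaluable number and at most about 76% with no loss. This rests on the plan's own rates, equal allocation, a chi-square comparison, and reading P < 0.05 with a 95% interval as two-sided. That 81 arose from leaving alpha at 0.05 in a one-sided calculation is an inference, but the mismatch does not depend on it. Because it concerns the trial's headline power claim, it must be corrected.

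**What to change.** Rewrite the sample-size paragraph so that it states:

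- 81 evaluable per arm gives 80% power only at one-sided 0.05, and about 70% at one-sided 0.025 / two-sided 0.05;
- 186 randomised, with 15% loss, gives about 69% power for a 15-point difference (76% with no loss), or 80% power for about 16.7 points;
- 103 evaluable per arm would be needed for 80% power at 15 points;
- 0.80 is the power, not beta.

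In the Statistical analysis section, say in words that the test is two-sided at 0.05, and keep the 95% interval. Do not move to one-sided 0.05 to justify the existing number: that would double the one-sided error rate the plan states.

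This costs wording only, and the stated power becomes less favourable. If recruitment is still open, the sponsor could instead raise the target to 244 randomised (103 / 0.85 per arm, rounded up), which is 244 − 186 = 58 more participants. The plan's assumption of 36 facilities with 6 patients each yields 216, so that option would also need more facilities or a longer recruitment period.

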**Methods:**

This study is a single-blind parallel-group design individual randomized control trial. A total of 186 participants (93 per group) will be individually randomized into one of the two groups with a 1:1 allocation ratio by a computer-generated algorithm. Group one (intervention) participants will receive daily SMS texts and weekly phone calls concerning their daily medication intake and medication refill clinic visit reminder and group two (control) participants will receive the same routine standard treatment care as the intervention group, but no SMS text and phone calls. All participants will be followed for two months of home-based self-administered medication during the continuation phases of the standard treatment period. Urine test for the presence of isoniazid (INH) drug metabolites in urine will be undertaken at the random point at the fourth and eighth weeks of intervention to measure medication adherence. Medication adherence will also be assessed by self-report measurements using the AIDS Clinical Trial Group adherence (ACTG) and Visual Analogue Scales (VAS) questionnaires, and clinic appointment attendance registration. Multivariable regression model analysis will be employed to assess the effect of the Ma-MAS intervention at a significance level of P-value < 0.05 with a 95% confidence interval.

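### The 15% attrition allowance is too small: 93 per arm leaves about 79 evaluable, not the 81 the plan requires

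*Protocol article*

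**What the plan says.** The Sample size section of the protocol article takes a control-group non-adherence rate of 0.256 and an intervention-group rate of 0.106. Its settings are given as "choosing a 95% confidence level (alpha = 0.05), 80% power (beta = 0.80) and a one-sided p-value of 0.025", which "for the initial sample size would yield n = 81 participants per arm". It then adds the allowance for losses: "Assuming an attrition rate of 15%, the final sample size would be a total of n = 186", with 93 in each arm. The abstract repeats the result: "A total of 186 participants (93 per group) will be individually randomized". The inflation formula is not shown, and nothing else in the article gives another reason for 93 per arm.

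**The concern.** An attrition rate is the share of randomised participants who are lost. The number to randomise is therefore the required evaluable number divided by one minus that rate. Multiplying by one plus the rate always gives too few, because the loss then falls on the enlarged group.

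The printed figures look like the second operation. If so, the requirement (81), the attrition rate (15%) and the final size (93) cannot all hold. At stake is the headline sample size, which also stands in the abstract: it would not deliver the evaluable number that the plan says it needs, under the plan's own assumption about losses.

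**Working it through.** **Inputs** (all from the Sample size section): control rate p₀ = 0.256; intervention rate pₐ = 0.106; difference 0.15; 80% power; 81 per arm before attrition; attrition 15%; 93 per arm and 186 in total after attrition.

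**1. Reproducing the plan's final figure.**
- Per arm: 81 × 1.15 = 93.15, printed as 93.
- In total: 162 × 1.15 = 186.3, printed as 186.

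Both match. The formula is inferred from this match, since the article does not print one.

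**2. The number needed to keep 81.**
- 81/(1 − 0.15) = 95.29, so 96 per arm and 192 in total.
- Worked on the total: 162/0.85 = 190.6, which also becomes 192 with equal arms.
- Gap from the plan: 96 − 93 = 3 per arm, 6 in total.

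**3. What 93 per arm delivers.**
- 93 × 0.85 = 79.05, so about 79 evaluable per arm (186 × 0.85 = 158.1 in total, against 162 required).
- Attrition at which 93 still leaves 81: 1 − 81/93 = 12.9%.

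**4. Effect on power.** The check uses the two-proportion z-test with pooled variance under the null and no continuity correction:

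n = [z_α √(2p̄(1−p̄)) + z_β √(p₀(1−p₀) + pₐ(1−pₐ))]² / (p₀ − pₐ)²

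with p̄ = (0.256 + 0.106)/2 = 0.181. The two square roots are √0.2965 = 0.5445 and √0.2852 = 0.5341.

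- One-sided 0.05: (1.645 × 0.5445 + 0.8416 × 0.5341)²/0.0225 = 80.4, so 81.
- One-sided 0.025 (two-sided 0.05): (1.960 × 0.5445 + 0.8416 × 0.5341)²/0.0225 = 102.2, so 103.

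With this test, the printed 81 is reproduced at one-sided 0.05 and not at the stated one-sided 0.025. Power is therefore shown at both levels, from Φ[(0.15√n − z_α × 0.5445)/0.5341]:

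| Evaluable per arm | One-sided 0.05 | One-sided 0.025 (two-sided 0.05) |
|---|---|---|
| 81 | 80.3% | 70.2% |
| 80 | 79.8% | 69.6% |
| 79 | 79.4% | 69.1% |

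The attrition step costs 0.9 points in the first column and 1.1 points in the second. The difference of about 10 points between the columns comes from the significance level and is not part of this point.

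**The case against.** The arithmetic is hard to dispute. The case against rests on size and on what else is wrong in the paragraph.

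- **The effect is very small.** Two evaluable patients per arm and about one point of power are minor beside the uncertainty in a round 15% attrition assumption. With simple randomisation of 186, the standard deviation of one arm's size is about √186/2 = 6.8, more than the gap. This stands as a comment on importance. It does not remove the shortfall in the total (158 against 162).
- **Most of the low power has another cause.** Power is already 70.2% with a full 81 per arm at the stated one-sided 0.025. This also stands, and only about 1 point should be charged to attrition.
- **Moving to 192 would not settle the sample size.** It holds a target of 81, which is itself too low at the stated level. With 103 as the base, 103/0.85 = 121.2, so 122 per arm and 244 in total. That exceeds the 36 × 6 = 216 patients the plan expects to find. This stands, and it limits the value of 192 as a remedy taken alone.
- **Intention to treat covers everyone randomised** (Statistical analysis section), so 93 rather than 79 might be analysed. This does not help much. The primary endpoint is a urine test at week eight, and a participant lost before then has no result. The plan's own allowance also treats losses as reducing the usable number.

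**Conclusion.** The point holds. An evaluable requirement of 81, a 15% loss and 93 randomised per arm are inconsistent: 93 leaves about 79, and 81 needs 96. The size is 3 per arm randomised (6 in total), 2 per arm evaluable, and about 1 percentage point of power. Even at one-sided 0.05, the level that reproduces 81, power at the plan's own attrition rate is 79.4%, just under the stated 80%.

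This rests on reading attrition as the share of randomised participants without a primary result, on equal arms and equal loss in both, and on the pooled two-proportion test without continuity correction. It is a numerical error worth correcting because the trial's headline number depends on it. It does not by itself threaten the trial.

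**What to change.** The minimum is a change of wording in the Sample size section. State that 186 randomised gives about 79 evaluable per arm at 15% attrition, or alternatively that 186 keeps 81 per arm only up to 12.9% attrition. Quote the power for 79 per arm at the significance level the analysis will use: 69.1% at one-sided 0.025 (two-sided 0.05), or 79.4% at one-sided 0.05. The abstract's 186 can stay. This costs nothing beyond the text.

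If the sponsor prefers to hold 81 evaluable per arm, the total becomes 192. That is six more participants, within the 216 the plan expects to be available.

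The sponsor should settle the significance level first, because it fixes the base number to be inflated. Whatever base results, the allowance should be applied by dividing by 0.85 and rounding up in each arm. With a base of 103, multiplying by 1.15 would give 118.5 per arm, whereas dividing by 0.85 gives 122, so the same error would carry over if only the significance level were corrected.
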